## Abstract

**Importance:**

Stable angina pectoris (SAP) often occurs in the elderly and is relatively stable for 1–3 months; however, if patients do not receive effective treatment, life-threatening acute myocardial infarction could occur. Patients with different clinical types of coronary heart disease have different intestinal flora. Baduanjin, a traditional Chinese Qigong, has been used as adjuvant therapy to improve the symptoms of patients with SAP.

**Objective:**

To determine the effect of Baduanjin exercise on the symptoms of patients with SAP and the intestinal flora, explore the action links and targets of Baduanjin intervention in elderly patients with SAP, and explain its mechanism.

**Design:**

A single-center, single-blind, randomized controlled trial. Patients and outcome assessors were blinded to group allocation.

**Setting:**

The trial will be conducted at Guang'anmen Hospital of China Academy of Chinese Medical Sciences.

**Participants:**

One hundred and eighty patients aged 60 to 80 years with stable angina pectoris (I–III) were intervened for 8 weeks and followed up for half a year.

**Interventions:**

Among the screened patients, 180 patients will be randomly assigned to either the Baduanjin or the control group at a 1:1 ratio (exercise duration: for 3–5 times a week, for 8 weeks) of moderate-intensity Baduanjin or free activities.

**Main and secondary results:**

The main result is the total effective rate for angina pectoris symptoms; secondary results include the duration of angina pectoris, number of angina pectoris episodes per week, nitroglycerin consumption, nitroglycerin reduction rate, Seattle angina score (SAQ), quality of life (SF-36),Traditional Chinese Medicine (TCM) syndrome scores, electrocardiogram (ECG) changes, blood lipid serum hypersensitive C-reactive protein levels, intestinal flora changes, serum changes in the intestinal flora metabolite Trimetlylamine oxide (TMAO), and non-targeted liposome detection. Adverse events will be recorded throughout the experiment, and the data will be analyzed by researchers who did not know about the assignment.

**Discussion:**

This study provides compelling evidence for at-home use of Baduanjin exercise to relieve SAP-associated symptoms.

**Trial registration:**

This study was approved by the ethics committee of Guang'anmen Hospital of China Academy of Chinese Medical Sciences (2022-121-KY). The trial has been registered in Chinese Clinical Trial Registration Center (ChiCTR2200062450).

## Introduction

Angina pectoris is a common cardiovascular disease seen in outpatient departments and is characterized by insufficient blood supply caused by coronary atherosclerosis, resulting in myocardial hypoxia and ischemia, followed by paroxysmal chest pain (1), precordial discomfort, and other symptoms, especially in the elderly (2). Chronic stable angina pectoris (SAP) is the most common subtype, and its clinical manifestations remain stable for ~1–3 months; however, without timely and effective diagnosis and treatment, it can easily develop into life-threatening acute myocardial infarction. Due to the symptoms caused by angina pectoris (e.g., chest pain), many elderly people restrict their daily activities, thereby leading to a relatively poor quality of life (1).

SAP was initially treated using percutaneous coronary intervention (PCI) (2). Annually, more than 500,000 patients with SAP undergo PCI. Clinical results from revascularization and active drug evaluation trials showed little difference in the incidence and mortality of myocardial infarction between patients with stable coronary heart disease who received coronary intervention and the control group (3). The benefits of coronary revascularization are limited to improving quality of life and cannot decrease the rate of cardiovascular events (4). Emphasis should be placed on optimizing lifestyle factors and preventative therapy, such as intake of lipid-lowering and antiplatelet drugs, to reduce the risk of cardiovascular events and death. Anti-angina drugs, such as β-receptor blockers, nitrates, or calcium channel blockers, should be started to improve the symptoms of angina pectoris (5). Phase I of a cardiac Rehabilitation (CR) program is recommended by the American Heart Association and the European Society of Cardiology as part of the comprehensive care for patients with coronary heart disease. In particular, exercise therapy has always been regarded as a core element (6–9). The results of a recent systematic analysis also support this view (10). However, the proportion of people over 60 years old participating in traditional CR is low (6, 11). Due to poor health and environmental barriers, most older people cannot meet the recommendations of the American Heart Association on physical activity for older people (12, 13). In the United States, <40% of elderly patients with coronary heart disease participate in CR (6).

Baduanjin is the most widespread ancient Chinese technique as it is a moderate-intensity-free activity, can be easily practiced, and is not restricted by venue (14, 15). Baduanjin comprises gentle and slow movements, combined with deep breathing and relaxation. Long-term exercise can strengthen health, bright ears and eyes, and prolong life. As a health-preserving method, Baduanjin has a 1,000-year history. It contains eight easy-to-learn movements and has a positive effect on all organs of the human body (16). Baduanjin can delay left ventricular remodeling in patients with myocardial infarction by improving energy metabolism and inhibiting inflammation (17). Additionally, it has a positive role in protecting vascular endothelial function, alleviating dyslipidemia, stabilizing blood sugar and blood pressure, and improving quality of life (18–22). Furthermore, short-term endurance exercise contributes to improving the richness of intestinal microflora (23).

Based on this background, we designed a single-center, single-blind, randomized controlled trial (RCT) to compare the efficacy and safety of 8 week Baduanjin exercise and moderate-intensity aerobic walking in elderly patients with SAP. We also assessed nitroglycerin reduction dose, angina pectoris frequency, Seattle angina pectoris score (SAQ), quality of life (SF-36), TCM syndrome score, ECG changes, blood lipids, serum hypersensitive C-reactive protein and intestinal flora changes.

## Materials and methods

### Design

This single-center, randomized controlled trial will be conducted in Guang'anmen Hospital of China Academy of Chinese Medical Sciences. After providing written informed consent, 180 participants will be randomly assigned to the medium-intensity Baduanjin or medium-intensity control groups (free activities). Medium-intensity is defined as energy consumption (calories) per unit time, which is 3 to 6 times higher than that during meditation. The intervention time will be 8 weeks, followed by 6 months of follow-up, and the results will be evaluated immediately at the end of the follow-up period. Figure 1 illustrates the flow of this experiment; the scheme of the clinical trial is in line with the standard program project: intervention trial guidelines recommend (24) and follow the comprehensive standards for reporting trials (25).

**Figure 1 F1:**
[figure not shown]
Flowchart of the clinical trial design.

### Recruitment

Through a series of recruitment strategies such as putting up posters in the hospital, patients will be recruited from the Department of Cardiology and Comprehensive Department of Guang'anmen Hospital. Researchers will communicate with potential patients and provide relevant information relating to the study, including the purpose, process, interventions, and potential adverse reactions. Researchers will screen the patients, and those who meet the inclusion criteria and volunteer to participate in the study will provide written informed consent.

### Study population

The diagnostic criteria for chronic SAP refers to the 2019 ESC guidelines for the diagnosis and management of chronic coronary syndromes (26).

#### Inclusion criteria

The inclusion criteria are as follows:

(1) Meet the SAP diagnostic criteria,(2) Age between 60 and 80 years old,(3) Classified as I–III based on severity, according to the Canadian Cardiovascular Society (CSS) grading of angina pectoris,(4) Sign the informed consent form.

#### Exclusion criteria

The exclusion criteria are the following:

(1) Severe arrhythmia and moderate cardiac insufficiency (EF <40%);(2) Uncontrolled hypertension, systolic blood pressure (SBP) ≥180 mmHg, and diastolic blood pressure (DBP) ≥100 mmHg;(3) Three-month recent history of AMI or PCI, coronary artery bypass grafting, severe trauma, and cerebrovascular accident;(4) Severe shock and primary organ diseases (such as of the liver, kidney, lung, etc.);(5) Obvious infection, fever, and severe anemia;(6) Severe joint disease;(7) Antibiotic use or participation in any antibiotic, probiotic, or laxative research in the 3 months preceding the study;(8) Gastrointestinal diseases such as diarrhea and ulcerative colitis in the past 2 months.

#### Criteria for withdrawal and removal

(1) Researchers will further exclude the following patients:① Those who were not suitable to continue with the trial;② Those with poor compliance, which affects their judgment of efficacy and safety;③ Those with disease progression to acute coronary syndrome;④ Those unable to perform Baduanjin exercises due to serious musculoskeletal problems.(2) Self-withdrawal is characterized as follows:① Unwillingness or inability to continue with the clinical trial for any reason;② Not explicitly intending to withdraw from the trial but no longer being treated and tested.

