### Sample size

The sample size was calculated according to the effective rate of the Baduanjin group and the control group. Referring to the previous research (27), it is assumed that the effective rate of the combination of traditional Chinese medicine and western medicine is 76.2%, and the effective rate of western medicine is 45.8%. Based on the class I error rate of α = 0.05 and the efficacy of 90% (II error rate of β = 0.1), bilateral test, and considering the shedding of 20%, the experiment was expanded to 69 people. Because the reference study is drug intervention, considering that this study is non-drug intervention, we continue to expand the sample size to 90 people in each group, a total of 180 people.

$$\begin{array}{l} n=\frac{{\left(u_{\alpha }+u_{\beta }\right)}^{2}\left(1+1/k\right)p\left(1-p\right)}{{\left(p_{e-}p_{c}\right)}^{2}} \end{array}$$

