### Data collection and management

If participants deviate from the intervention program, additional participants will be included to minimize data loss during the study period. Patients will be supervised and guided by specialized researchers throughout the intervention. At the fourth and eighth weeks, participants will be required to return to the hospital for scale (Such as clinical symptoms, SAQ and TCM syndrome scores) or clinical-related tests, and regular telephonic follow-up will be conducted by researchers during the follow-up period. Researchers remind patients to undergo daily moderate-intensity training, and those who deviate from the intervention plan will receive telephonic reminders, to ensure the integrity of the study data.

Basic patient information and relevant information required for the study will be recorded in the printed case report form (p-CRF). The patient's medical records (medical records, test sheets, etc.) will be stored in the hospital, and the doctor records the patient's test results in the observation medical records. Only authorized researchers, ethics committee members, and relevant research management department members will be able to access patient records following reasonable request. The name and identity of the patient will not appear in the study and published papers. The research team will do everything possible to protect the privacy of patients' personal medical data from disclosure within the scope permitted by law.

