### Statistical analysis

A full-analysis set (FAS), per-protocol analysis set (PPS), and safety analysis set (SAS) will be created according to the principle of intentional therapy (34). FAS participants are identified as those who received at least one exercise. Those who adhere to the treatment plan but changed groups midway are part of the PPS. For safety indicator assessment, researchers will use the SAS to analyze the incidence of adverse events and laboratory indicators. Statistical analysis will be conducted by third-party statisticians blinded to experimental grouping and intervention methods, using SPSS 25. We will analyze the baseline demographic data to determine the comparability between the two groups. Mean ± standard deviation will be used for continuous variables that conform to normal distribution, and median and quartile methods will be used for continuous variables that do not conform to normal distribution. The Chi-square test or Fisher's exact test will be used to compare classified counting data. The paired *t*-test will be used to compare differences within the group, and the independent-sample *t*-test will be used to compare differences between groups. If the data do not conform to normal distribution, a Wilcoxon paired test and Mann-Whitney U test will be used to analyze intra- or inter-group differences. *P* < 0.05 is considered as statistically significant.

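### Post-randomisation removal, replacement of deviators and a one-session FAS rule contradict the stated intention-to-treat principle and can bias the total effective rate in either direction

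*Protocol article*

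**What the plan says.** Four sections of the protocol article decide who is counted.

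- **Criteria for withdrawal and removal.** Beyond the eligibility exclusions, researchers may exclude patients in several categories, among them "Those with poor compliance, which affects their judgment of efficacy and safety", "Those with disease progression to acute coronary syndrome" and "Those unable to perform Baduanjin exercises due to serious musculoskeletal problems". Compliance and progression are events during the trial. The section names no analysis set.
- **Data collection and management.** "If participants deviate from the intervention program, additional participants will be included to minimize data loss during the study period". The number of added participants, their arm and their route of entry are not given.
- **Statistical analysis.** The analysis sets are said to follow the intention-to-treat principle, but "FAS participants are identified as those who received at least one exercise".
- **Primary outcome, note under Table 3.** The total effective rate divides the patients in the two favourable categories by a sample size that is not defined.

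The Randomization and blinding section adds that researchers open the envelopes after enrolment, and that researchers, participants and coaches cannot be blinded.

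**The concern.** The primary outcome is a responder proportion, so membership of the denominator acts directly on the result. Intention to treat protects the comparison because membership is fixed at randomisation. Here it can depend on later events.

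- Whether a patient starts exercising is settled after the arm is known.
- Compliance is judged by staff who know the arm.
- Progression to acute coronary syndrome (ACS) is an unfavourable course in a stable angina trial. The Introduction itself names acute myocardial infarction as the danger. Excluding such patients from the efficacy analysis would take failures out of the denominator.
- Inability to perform Baduanjin will in practice come to light mainly in the arm asked to perform it.
- Adding participants does not repair the loss, because the newcomers are different people from those removed after allocation.

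If the arms lose failures at different rates, the difference in total effective rate no longer estimates the effect of assignment, and the test no longer has its nominal error rate.

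**Working it through.** **1. The plan's own figure.** Inputs from the Sample size section: rates of 76.2% and 45.8%, 20% shedding, and "Based on the class I error rate of α = 0.05 and the efficacy of 90% (II error rate of β = 0.1), bilateral test". The mean rate is p = (0.762 + 0.458)/2 = 0.61, and k = 1.

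n = (1.960 + 1.282)² × 2 × 0.61 × 0.39 / 0.304² = 10.507 × 0.4758 / 0.0924 = 54.1, rounded up to 55.

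55 / 0.80 = 68.75, rounded up to 69. The stated 69 therefore reproduces as a number per group. The step from 69 to 90 per group is a judgement, not a calculation.

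**2. What happens to a removed patient.** Take a patient who completes one session and then has ACS. Under the FAS definition alone, that patient stays in. Under the withdrawal criteria, that patient is excluded, from what is not said. The denominator under Table 3 does not settle it. A patient who never starts is outside the FAS on any reading, although intention to treat would keep that patient. The per-protocol set is no clean fallback, since as worded it takes in patients who switched groups.

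**3. Size of possible bias.** The documents give no removal rates beyond 20% overall shedding, so the rates r below are assumptions. Assume also no true effect, 45.8% effective in both arms, 90 per arm, every removed patient a failure, and removed patients absent from the analysis. The observed rate in an arm becomes 0.458/(1 − r).

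For retained rates q1 and q2 with difference d, the rejection probability of the two-sided test is 1 − Φ((1.96·SE0 − d)/SE1) + Φ((−1.96·SE0 − d)/SE1), with SE0 pooled and SE1 unpooled. This treats the retained patients as independent samples at the shifted rates.

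Removal from the Baduanjin arm only:

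| r | Baduanjin rate | Spurious difference (points) | Type I error | Type I error if refilled to 90 |
|---|---|---|---|---|
| 5% | 48.2% | +2.4 | 6.2% | 6.2% |
| 10% | 50.9% | +5.1 | 10.2% | 10.5% |
| 20% | 57.25% | +11.45 | 30.4% | 33.5% |

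Worked line for 10%: n1 = 81, q1 = 0.458/0.90 = 0.5089, n2 = 90, q2 = 0.458, d = 0.0509, SE0 = 0.0765, SE1 = 0.0764, which gives 0.102.

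Removal from control only gives the same sizes with the opposite sign. Equal removal from both arms gives no difference and a type I error of 5%.

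**4. If the planned effect is real.** Equal removal of failures then inflates the difference to 30.4/(1 − r): 32.0, 33.8 and 38.0 points at 5%, 10% and 20%.

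**5. Power with everyone kept.** Count removed patients as failures in both arms, so each planned rate is multiplied by (1 − r), with 90 per arm.

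| r | Rates | Power |
|---|---|---|
| 5% | 72.4% v 43.5% | 98.0% |
| 10% | 68.6% v 41.2% | 96.4% |
| 20% | 61.0% v 36.6% | 91.1% |

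**The case against.** The strongest reply is that the rules are neutral on their face. No criterion is confined to one arm, both arms exercise under supervision in hospital, and equal removal does no harm under the null. A reader might infer that the rules as a whole favour Baduanjin, and the documents do not support that. Only the Baduanjin-inability criterion has a likely direction, and severe joint disease is already an eligibility exclusion, which should make it uncommon. If ACS were more frequent in controls, removing it would work against Baduanjin.

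Three further inferences go too far.

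- **Removed patients certainly leave the FAS.** The text does not say so. A patient with one session would stay in under the FAS definition. The defect is that both readings are open to staff who know the arm.
- **ACS disappears from the trial.** The Abstract has adverse events recorded throughout, Table 1 schedules them, the safety set analyses their incidence, and the Safety assessment section sends adverse events to the Ethics Committee and the monitoring board. What may be lost is ACS as a failure in the efficacy comparison.
- **Added participants are chosen for adherence.** No such selection is described, and deviators are said to receive telephone reminders.

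The Abstract also says that patients and outcome assessors are blinded. The methods section rules out blinding of participants and researchers, and it is the researchers who apply the removals.

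Handling of missing data is commonly left to an analysis plan that is not shown. The point here rests on what the article states: an FAS narrower than all randomised, exclusion after randomisation, and replacement.

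**Conclusion.** The contradiction stands. An intention-to-treat principle is claimed beside three rules that let the analysed population depend on events after allocation, in a trial where those applying the rules know the arm. The direction of bias is open in general and likely towards Baduanjin for one criterion.

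The figures of about 6%, 10% and 30% for type I error show what is possible. They are not a forecast: they require removal from one arm only, failures only, and loss from the analysis. The 20% case borrows the plan's shedding allowance, which is overall and tied to no arm or outcome. Because the rules govern the primary comparison and the remedy is wording, this should be corrected. Recruitment has already begun, so it should be done before removals and additions accumulate.

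**What to change.** - Define the FAS, and the denominator under Table 3, as all randomised patients in their assigned arm.
- State that the events listed under withdrawal and removal do not end outcome follow-up or inclusion in the analysis.
- Classify patients with ACS as not effective in the primary outcome, and also report ACS by arm.
- Count missing outcomes as not effective in the primary analysis. This is one defensible choice among several, so add a sensitivity analysis.
- Delete the replacement sentence. The sample size already allows 20% shedding and was then raised from 69 to 90 per group.
- Leave the clinical criteria for stopping exercise as they are, and reconcile the withdrawal, data-management and statistical sections.

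**Cost.** Wording changes in those sections and under Table 3, outcome collection from patients who stop exercising, and somewhat less favourable effective rates. No extra patients are needed: on the plan's assumed rates, power is about 98%, 96% and 91% when 5%, 10% and 20% of each arm are counted as failures.

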### Randomization and blinding

Participants will be randomly assigned to the Baduanjin or control groups with a proportion of 1:1, using a random number grouping table generated according to the number of assigned cases and random proportion. The random number table will be generated by using SAS 9.0, emergency letter preparation will be completed by people not involved with this clinical trial, and grouping information will be kept in a sealed, opaque envelope. The order of recruitment of participants is natural, and after enrollment, the researchers will open the envelopes in turn to determine the patients' grouping information.

In view of the different forms of intervention, blinding of the researchers, participants, and coaches throughout the experiment is not feasible. However, the laboratory technicians and researchers conducting the statistical analysis will remain blinded.

### Intervention

#### Baduanjin group

The Baduanjin group participants will focus on practicing at the Guang'anmen Hospital. During hospitalization, researchers guided and supervised the exercise, and after discharge, special researchers will supervise telephonically or through WeChat. Based on basic Western medicine treatment and health education, patients will perform eight stages of brocade exercise. Each exercise lasts about 30 min, including 5 min of warm-up exercise, 20 min of Baduanjin exercise, and 5 min of relaxation activities, lasting for 8 weeks, 3–5 times a week. The training program was formulated according to the “Baduanjin of Fitness Qigong,” issued by the State Administration of Sports in 2003, with a total of 10 postures (Figure 2). Participants should not be exercising extra.

